## Study procedure*s*

### Breath-Hold Assessment

All participants undergo protocolled education with ABC, then an assessment to confirm their ability to ABC-BH (Fig. 2a–c: ABC Device). Participants are screened for eligibility in IBH, DIBH and EBH in random order to reduce risk of bias, using a pre-determined block randomization sequence. Eligibility, breath-hold time (T_BH_) and ABC-BH threshold are recorded for each technique.

*T*_*BH*_ Time (seconds) that the participant can BH comfortably, at least three times.

*ABC-BH Threshold* Volume of air (liters) in the participant’s lungs at BH activation. The radiation therapists determine the threshold with the participant, as follows:

*EBH* 0.0–0.2 L*IBH* Peak volume of air during normal, relaxed respiration. Average of three measurements.*DIBH* Maximum peak volume of air during voluntary deep inspiration. Threshold is 80% of average of three measurements.

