### Pre-planning reproducibility and stability

To assess R_BH_ of tumor position between consecutive BHs, and S_BH_ of tumor position during each BH, 5 kV X-ray fluoroscopy images are acquired in each BH technique on an Elekta™ linear accelerator, using the XVI™ software “MotionView” function. The position of the tumor, or an appropriate surrogate (diaphragm or fiducial marker), is tracked. Each image is acquired anterior–posteriorly (AP) (Fig. 3), for the complete duration of each of the participant’s BH’s. R_BH_ and S_BH_ are defined as follows:*R*_*BH*_ Cranio-caudal position of the tumor/surrogate at the beginning of BH1 is compared to the position at beginning of BH2-5. Four observations are recorded per technique. The absolute value (ignoring direction) of the cumulative sum of each observation is determined, and then averaged.*S*_*BH*_ Cranio-caudal displacement of the tumor/surrogate, during each BH. Five observations are recorded per technique. The mean of the absolute value (ignoring direction) of each observation is then calculated.

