### Determination of treatment technique

Following the ABC-BH and pre-planning R_BH_ and S_BH_ assessments, selection of treatment technique is made according to the decision matrix (Fig. 4), with R_BH_ prioritized. If two or more techniques have equal (to nearest mm) mean R_BH_, then the technique with better S_BH_ is selected. A technique with mean R_BH_ and/or S_BH_ > 5 mm will proceed to free-breathing.

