### Planning reproducibility

Participants have all subsequent planning and treatment using the chosen BH technique. Four planning computed tomography (CT) scans are acquired for each participant. The scans are acquired sequentially within a 5 min timeframe, with no patient-repositioning between scans, to minimize the impact of repositioning or physiological variation. The Gross Tumor Volume (GTV), tumor surrogates and OARs are contoured on the first planning CT. Post-processing and measurements are completed using a customized workflow in MIM Maestro® software (MIM Software Inc, Cleveland OH). The first planning CT is automatically fused to subsequent CTs. Initially, a bone algorithm fusion corrects any gross patient misalignment. Then, a tumor, surrogate or fiducial marker fusion corrects for tumor/organ position. Contours are automatically generated onto each subsequent CT. Resultant contours are reviewed, and manually edited if required to account for deformation. The inter-BH displacement of the tumor and OARs are measured, with bone fusion as the starting position. Planning R_BH_ of tumour/surrogate and OARs is defined as follows:*R*_*BH*_ Position, in three planes, of the tumor/surrogate or OAR contour centroid and contour surface in CT1 compared to the position in CT2-4, resulting in three observations. The mean of the absolute values of the cumulative sum of each observation will be calculated.

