## Statistical analysis

Sample size calculation indicates required recruitment of 14–27 participants to be powered to detect a 2 mm variation in reproducibility, assuming standard deviation of 2 mm or 3 mm respectively.

The R_BH_ and S_BH_ measurements during pre-planning will be collated and described for each participant and each BH method. The number of patients screened into each BH technique will be reported, along with descriptive statistics such as the mean and standard deviation (SD) for R_BH_ and S_BH_ in order to compare each technique. Paired *t* tests will be used to test for differences between the BURDIE-screened R_BH_ and S_BH_ with our institutional standard technique EBH, including subset analysis of those participants who do not screen into EBH. Further comparisons will be made to compare each BH technique’s mean R_BH_ and S_BH_ with the selected technique mean. Mixed effects models will be used to evaluate the multiple observations for each patient, and each technique.

The planning mean R_BH_ measurements will be compared with the pre-planning results for each participant, and allow an assessment of the correlation between the mean R_BH_ values at the two time-points. Paired *t* tests will be conducted to provide an estimate of the 95% confidence interval in the paired observations with a margin of ± 2 mm considered to reflect similarity and/or an indication of the non-inferiority margin. Bland–Altman plots, with Pitman’s test will be prepared to test for any indication of bias in the pre-planning and planning R_BH_ means. Tests for variation across each BH technique will be conducted, with assessments of the average R_BH_ values for each technique, the study population and comparisons to the pre-planning time-point.

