To evaluate treatment R_BH_, correlation coefficients will be estimated as fixed-effects, to indicate the consistency between the inter-fraction and intra-fraction observations. The treatment mean R_BH_, will be compared to the pre-planning and planning results, and allow an assessment of the correlation between these paired means. The 95% confidence interval in the paired observations will be compared to a non-inferiority margin of ± 2 mm, with Bland–Altman plots and the Pitman’s test used to test for any indication of bias in the treatment R_BH_ for comparison with pre-planning and planning means. However, it is expected that that the difference between the pre-planning, planning and treatment values may reduce over time, and these differences will be assessed descriptively, and compared to the non-inferiority margin of ± 2 mm.

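### The pre-planning R_BH paired with planning and treatment R_BH is the value that won the technique selection, so the paired mean difference and Bland–Altman bias show a spurious worsening

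*Protocol article*

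**What the plan says.** Under Pre-planning reproducibility and stability, R_BH for each technique compares the first breath-hold with the next four: "Four observations are recorded per technique". Three techniques are candidates: "Participants are screened for eligibility in IBH, DIBH and EBH in random order to reduce risk of bias".

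Under Determination of treatment technique, "selection of treatment technique is made according to the decision matrix (Fig. 4), with R_BH_ prioritized". The tie rule is: "If two or more techniques have equal (to nearest mm) mean R_BH_, then the technique with better S_BH_ is selected". A cut-off acts on the same measurements: "A technique with mean R_BH_ and/or S_BH_ > 5 mm will proceed to free-breathing".

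Under Planning reproducibility, "Participants have all subsequent planning and treatment using the chosen BH technique". Planning R_BH comes from new CT scans, and treatment R_BH from cone-beam CT at each fraction.

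The Statistical analysis section then pairs the time points. For planning: "The planning mean R_BH_ measurements will be compared with the pre-planning results for each participant, and allow an assessment of the correlation". Paired t tests supply a 95% confidence interval, judged against ±2 mm as similarity or non-inferiority, and Bland–Altman plots with Pitman's test look for bias. For treatment: "The treatment mean R_BH_, will be compared to the pre-planning and planning results, and allow an assessment of the correlation between these paired means". The same margin, plots and test apply. The section describes no separate baseline taken after selection, no split of the five breath-holds, and no other correction for selection.

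**The concern.** Each technique's pre-planning mean is its true R_BH plus measurement error. Choosing the technique with the lowest mean favours negative errors, so the chosen technique's recorded value is on average below its true value. The 5 mm cut-off trims high values in the same direction. Planning and treatment values are fresh measurements that played no part in the choice. If true R_BH stays the same, the expected difference (later minus pre-planning) is therefore positive rather than zero.

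The paired mean difference and the Bland–Altman bias are the quantities affected. A reader would take a positive difference, or an interval that excludes zero, as evidence that reproducibility seen at screening was lost by planning or treatment, when part or all of it is regression to the mean.

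**Working it through.** **Inputs.** From the document: three techniques; four observations per pre-planning mean; three per planning mean; selection on R_BH to the nearest mm, with S_BH breaking ties; margin ±2 mm; 14–27 participants. Assumed: the SD of breath-hold position within a participant and technique. The nearest figure is the Background's 1.5 mm cohort R_BH for expiration breath-hold with the breathing coordinator.

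**The plan's sample size.** For a paired t test to detect 2 mm with SD 2 or 3 mm, two-sided 5% and 90% power give 13 and 26. Two-sided 0.05/3 and 80% power give exactly 14 and 27. The article states neither alpha nor power. The point does not depend on this; 14 and 27 serve only as trial sizes.

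**Direction and order of size.** For three equally good techniques with normal errors, E[lowest of three] = true mean − 0.846 × error SD of a technique mean.

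| Error SD (mm, assumed) | Selected mean too low by (mm) |
|---|---|
| 0.5 | 0.42 |
| 1.0 | 0.85 |
| 1.5 | 1.27 |
| 2.0 | 1.69 |

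**Simulation of the protocol's rule.** R_BH was taken as the mean absolute displacement from the first hold, with holds independent and normal. Then true R_BH = 2 × SD/√π = 1.128 × SD. An SD of 1.33 mm gives 1.128 × 1.33 = 1.50 mm, matching the Background figure; 2.5 mm gives 2.82 mm. The chosen technique was measured again with no true change. For three equal techniques:

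| Result | SD 1.33 mm | SD 2.5 mm |
|---|---|---|
| Spurious shift | +0.44 mm (1.06 to 1.50) | +0.99 mm |
| Paired t test rejects zero, N=14 | 39% | 57% |
| Paired t test rejects zero, N=27 | 73% | 88% |

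Adding real differences between participants and between techniques within participants (log-SD 0.3 each) lowers the rejection rates. Over all these settings they run from about 29% to 57% at N=14 and from 59% to 88% at N=27. A technique fixed in advance gives 4–6%. Two readings of R_BH that use the cumulative sum gave 41–67% (N=14) and 75–96% (N=27), so the result does not hang on how that definition is read.

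**The decision the plan names.** The upper 95% limit exceeds +2 mm in:
- 0–2% of trials at SD 1.33 mm;
- about 37–42% (N=14) and 16–19% (N=27) at SD 2.5 mm.

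**Pitman's test.** With SD 1 to 3 mm, it indicates larger variance at planning in 41–92% of trials with the selected baseline, against 9–16% with an independent one.

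**Control.** With pre-planning holds that took no part in the selection, the mean difference is within ±0.01 mm of zero, and planning is called significantly worse in 2.1–2.7% of trials (nominal 2.5%).

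**The case against.** The strongest reply is that the rejection rates concern a decision the plan does not make. The article states no null of zero difference as its decision rule. It uses the paired t test to obtain an interval and reads that interval against ±2 mm; for treatment it names no t test and says the differences will be assessed descriptively. This stands. At the only SD tied to a figure in the document, the margin conclusion is essentially untouched, and any error works against a non-inferiority claim. A reader might infer that the trial would wrongly declare reproducibility lost beyond its margin. That is supported only at larger SDs, which the document does not give.

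A reader might also infer that primary outcomes c and d are biased. They are not: Primary outcome measures defines them as R_BH at planning and at treatment in the selected technique. Those are levels measured after selection.

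The simulation is also idealised. Pre-planning R_BH is cranio-caudal fluoroscopy, whereas planning and treatment R_BH are three-plane CT and cone-beam CT. That separate difference could add to the shift or mask it, but does not remove it. Not every participant need have three eligible techniques, and the shift becomes small when techniques truly differ a lot. With between-technique SD 2 mm and error SD 0.5 mm, the normal model gives 0.10 mm.

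None of this touches the mechanism. The plan itself looks for bias with Bland–Altman plots on these pairs, and they would display the artefact.

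**Conclusion.** The concern holds for the paired mean difference from pre-planning, its confidence interval and the Bland–Altman and Pitman assessments. The direction follows from the protocol's own selection and pairing rules. The size is conditional: about 0.4 to 1.0 mm for assumed hold SDs of 1.33 to 2.5 mm, or roughly 20–50% of the 2 mm margin, and less if techniques differ greatly within participants. The ±2 mm conclusion is at risk only towards the upper end of that range, and then in the conservative direction. The comparison of planning with treatment is free of this effect, since both follow selection.

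**What to change.** Two changes to the Statistical analysis section:

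1. State that uncorrected differences from pre-planning include regression to the mean caused by selection and are not to be read as lost reproducibility. Rely on the planning-versus-treatment comparison, already planned, as the selection-free check of change, and note that its modalities and time frames also differ. It does not replace the pre-planning question.
2. For the group mean difference and its 95% confidence interval against ±2 mm only, add a selection-corrected pre-planning mean from the existing five images. Apply the selection rule to three holds, measure displacement between the two held-out holds in the technique so chosen, and average over the ten possible splits. In simulation this leaves a shift of −0.08 to +0.02 mm and rejection of 5–7%.

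Keep the treated technique's own pre-planning value for the per-participant correlation and the Bland–Altman plots, with the selection caveat attached.

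The cost is analysis wording and a short program, with no new images or patients. The corrected mean is noisier and gives up the first breath-hold as the fixed reference. About 35–40% of splits choose a technique other than the one treated, so it is valid for the group mean and not as a participant's paired value. It does not correct for the difference between fluoroscopy and three-plane CT. The selection rule used for care is unchanged.

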### Treatment reproducibility

Intra-fraction and inter-fraction R_BH_ is measured for each participant. For all treatment fractions, 3D volumetric Cone Beam Computed Tomography (CBCT) images are acquired using Elekta XVI™ (Elekta, Stockholm, Sweden) before treatment delivery. For participants treated with SABR, post-correction, during, and post-treatment CBCTs are also acquired. Each CBCT is a 360° acquisition using several BHs, with acquisition paused between BHs. The CBCT is automatically fused to the planning CT with a bone algorithm to correct patient setup. Then, a soft-tissue fusion corrects for tumor position. Tumor displacement is measured as the correction applied after accounting for patient setup. Treatment R_BH_ of tumour is defined as follows:*Inter-Fraction R*_*BH*_ Position, in three planes, of the tumor/surrogate on planning CT compared to the position on CBCT1, at each treatment fraction. Results will be collated for all fractions, and averaged.*Intra-Fraction R*_*BH*_ For those participants with multiple CBCTs per fraction, the position, in three planes, of the tumor/surrogate on CBCT1 compared to the position on each subsequent CBCT, at each treatment fraction. The mean values of the absolute value of the cumulative sum of each observation will be calculated.

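### The planned correlation of inter-fraction with intra-fraction R_BH has CBCT1 on both sides, so its null value need not be zero and it cannot be read as consistency

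*Protocol article*

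**What the plan says.** Protocol article, Treatment reproducibility, defines two measures:

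- Inter-fraction R_BH is the position "of the tumor/surrogate on planning CT compared to the position on CBCT1, at each treatment fraction". The stated summary is "Results will be collated for all fractions, and averaged".
- Intra-fraction R_BH is the position "of the tumor/surrogate on CBCT1 compared to the position on each subsequent CBCT, at each treatment fraction". The stated summary is "The mean values of the absolute value of the cumulative sum of each observation will be calculated".

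Repeat imaging within a fraction is described for one group: "For participants treated with SABR, post-correction, during, and post-treatment CBCTs are also acquired".

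For the treatment stage, the first analysis named in the Statistical analysis section is that "correlation coefficients will be estimated as fixed-effects, to indicate the consistency between the inter-fraction and intra-fraction observations". The section mentions neither the shared scan nor a reference value other than zero. Inter-fraction and intra-fraction R_BH at treatment are primary outcome (d).

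**The concern.** CBCT1 is one end of both differences. If the breath-hold on CBCT1 is atypical, or that scan is registered with error, the distance from the planning CT and the distance to the later CBCTs both change. Two quantities built this way are correlated by construction. A reader who takes zero as the value for no relation, and a positive coefficient as a sign of consistency, could credit the technique with something the arithmetic produced.

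The coefficient also depends on how variable the planning CT, the fractions and the CBCTs are relative to each other. These ratios are unknown in advance, so the coefficient has no fixed benchmark.

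**Working it through.** The plan gives no figure for this correlation, so there is none to reproduce. The sample size statement ("required recruitment of 14–27 participants to be powered to detect a 2 mm variation in reproducibility") does not bear on it and is used below only for participant numbers.

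**Inputs.** From the document: the two definitions, and up to three kinds of later CBCT per SABR fraction, so K = 1 to 3. Assumed: normal, independent positions on one axis; the variance ratios; 3 or 5 fractions.

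**Notation.** P is the position on the planning CT, C1 on CBCT1, Ck on a later CBCT. σP² is the variance of P, σ² the scan-to-scan variance of a CBCT within a fraction, and σF² the variance of a real between-fraction shift, which is common to C1 and Ck.

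**Signed differences in the document's order**, P − C1 against C1 − mean(Ck):

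- Covariance = −σ², because only the scan noise of C1 is shared
- Var(P − C1) = σP² + σF² + σ²
- Var(C1 − mean Ck) = σ²(1 + 1/K)
- ρ = −σ² / √[(σP² + σF² + σ²) · σ²(1 + 1/K)]

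With σP = σ = 1 and σF = 0:

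- K = 1: −1/√(2 × 2) = −0.50
- K = 2: −1/√(2 × 1.5) = −0.58
- K = 3: −1/√(2 × 4/3) = −0.61

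**Absolute values.** For bivariate normals with mean zero, corr(|X|,|Y|) = (2/π)[ρ·asin ρ + √(1 − ρ²) − 1] / (1 − 2/π).

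- ρ = 0.50: 0.6366 × (0.2618 + 0.8660 − 1) / 0.3634 = 0.22
- ρ = 0.612: 0.6366 × (0.4036 + 0.7906 − 1) / 0.3634 = 0.34

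The second figure takes the absolute value after combining the three later CBCTs. Taking the mean of the three absolute values instead gives 0.32 by simulation.

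**Sensitivity, absolute values per fraction (simulated):**

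| Situation, no real relation | K = 1 | K = 3 (mean of absolutes) |
|---|---|---|
| Planning CT and CBCT equally variable | 0.22 | 0.32 |
| CBCT averages 2 breath-holds, planning CT one | 0.15 | 0.21 |
| CBCT averages 5 breath-holds, planning CT one | 0.07 | 0.11 |
| Equal variability, real fraction shift with SD 1σ | 0.15 | 0.21 |
| Same, shift SD 2σ | 0.07 | 0.11 |
| Same, shift SD 3σ | 0.04 | 0.06 |

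If a CBCT averages m breath-holds, σ² = 1/m and σP² = 1, so the signed value is −1/√[(m + 1)(1 + 1/K)]. For m = 2 to 5 this is −0.41 to −0.29 with K = 1 and −0.50 to −0.35 with K = 3.

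**Mixed scale.** With a signed inter-fraction value and an absolute intra-fraction value, reversing the sign of every deviation reverses the first and leaves the second unchanged. The covariance is therefore zero, and simulation gives 0.00.

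**Participant means** (K = 3, equal variability, absolute values): +0.27 with 3 fractions and +0.23 with 5.

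**Illustration of consequence.** Suppose every participant had three later CBCTs per fraction at equal variability, and absolute values were tested with a simple Pearson test at 5%. In pure noise, p < 0.05 occurs in 54% of trials (14 participants, 3 fractions) to 93% (27 participants, 5 fractions) at fraction level, and in 15% to 28% using participant means. The document does not prescribe either test.

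**Removing the shared scan.** If the intra-fraction measure uses only differences among the later CBCTs, the absolute-value correlation in pure noise is 0.00.

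**The case against.** Several counter-arguments stand in whole or part.

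- **Size.** A reader might infer a built-in correlation of 0.46 (one later CBCT) or 0.66 (mean of three). Those values need a planning CT that sits exactly at the mean position. Planning reproducibility has contours drawn on the first of four scans and treats differences between scans as breath-hold displacement, so the reference carries noise. Each CBCT is acquired over several breath-holds, which lowers the figure further.
- **Direction.** A reader might infer that noise would always look like consistency. That holds only if both measures are absolute. The document states absolute values for the intra-fraction measure and not in the inter-fraction sentence. The signed artefact is negative in the document's order, and the mixed scale has none.
- **Clustering.** A reader might infer that fractions are pooled without regard to participant, giving too narrow an interval. The phrase about fixed effects is unclear and may refer to a mixed model. The same section plans mixed models for multiple observations per patient, in its pre-planning paragraph. Nothing says that fractions are pooled.
- **Magnitude in mm.** A reader might infer that the treatment outcome is left without a size. It is not: mean R_BH is reported and compared with the earlier stages, with 95% confidence intervals against ±2 mm and Bland–Altman plots. No stated decision rests on the correlation.

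The core is untouched. The definitions share CBCT1, and the sentence reads the coefficient as consistency. More detail elsewhere on the model would not change that unless a definition, the scale or the reference value changed too.

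**Conclusion.** The point holds in a limited form. In participants with several CBCTs per fraction, the planned coefficient does not have a null value of zero when both measures are on the same scale.

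In pure noise, with a planning CT at least as variable as a CBCT, it is about +0.1 to +0.3 on absolute values and about −0.3 to −0.6 on signed differences in the document's order. It shrinks towards zero as real between-fraction shifts grow. It is 0 for a signed inter-fraction value against an absolute intra-fraction value.

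These figures assume independent normal positions on one axis. The variance ratios, the number of breath-holds per CBCT and the number of fractions are assumptions, because the document does not fix them.

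The artefact is modest and leaves the planned means and intervals intact. It does make this one statistic uninterpretable as a measure of consistency, within a primary outcome, and the sentence should be changed.

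**What to change.** In the treatment paragraph of the Statistical analysis section, replace the correlation with a mixed model, fitted per plane, of bone-referenced tumour displacement from the planning CT on each CBCT. The model should contain:

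- an overall mean offset, which keeps the systematic planning-to-treatment shift that the inter-fraction outcome is defined by;
- a random participant effect, which also absorbs the noise of that participant's planning CT;
- a random effect of fraction within participant;
- residual variation of CBCT within fraction, informed by participants with repeat CBCTs.

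Report the mean offset and the between-participant, inter-fraction and intra-fraction SDs in mm with 95% CIs, alongside the planned mean R_BH summaries.

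If a correlation is kept, state whether each measure is signed or absolute. Then either compare the coefficient with the non-zero value expected from the shared CBCT1, or compute the intra-fraction measure without CBCT1.

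The cost is one sentence of text and slightly more analysis work on displacements already measured. With 14 to 27 participants, and fewer with repeat CBCTs if not all receive SABR, the variance components will be imprecise. The intervals will show that.

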**Methods:**

Patients planned for radiation therapy to upper abdominal tumors are invited to participate in this prospective study. Participants attempt three breath hold techniques: inspiration, deep-inspiration and expiration breath-hold, in random order. kV fluoroscopy images of the dome of diaphragm are taken of five consecutive breath-holds in each technique. Reproducibility and stability of tumour position are measured, and used to select the technique with which to proceed to planning and treatment. Reproducibility at planning and each treatment fraction is measured, along with breath hold time, treatment efficiency and patient experience.

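### R_BH is a different quantity at pre-planning, planning and treatment, so holding paired differences against one ±2 mm margin can mistake a measurement difference for a change, or no change, in reproducibility

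*Protocol article*

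**What the plan says.** The protocol article uses the single name R_BH for four measurements.

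- **Pre-planning** (Pre-planning reproducibility and stability): "Cranio-caudal position of the tumor/surrogate at the beginning of BH1 is compared to the position at beginning of BH2-5". This is one axis, from AP fluoroscopy, with four observations per technique. The tracked structure is the tumor or a surrogate (diaphragm or fiducial). The abstract mentions only the diaphragm: "kV fluoroscopy images of the dome of diaphragm are taken of five consecutive breath-holds".
- **Planning** (Planning reproducibility): "Position, in three planes, of the tumor/surrogate or OAR contour centroid and contour surface in CT1", compared with CT2 to CT4. This gives three observations within 5 minutes, without repositioning.
- **Treatment, inter-fraction** (Treatment reproducibility): planning CT against the first CBCT of each fraction, in three planes, averaged over fractions.
- **Treatment, intra-fraction** (same section): first CBCT against later CBCTs of the fraction, in three planes, only where a participant has several CBCTs per fraction. On the scans themselves: "Each CBCT is a 360° acquisition using several BHs, with acquisition paused between BHs".

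The Statistical analysis section pairs these. Planning and pre-planning means are compared by paired t tests, with the 95% interval read against ±2 mm. For treatment: "The treatment mean R_BH_, will be compared to the pre-planning and planning results, and allow an assessment of the correlation between these paired means". The paired 95% interval is again held against a ±2 mm non-inferiority margin, with Bland–Altman plots and Pitman's test. The section expects the differences between time-points to shrink over time.

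**The concern.** A paired difference shows change over time only if the same thing is measured on both occasions. Here the axis, the image type, the landmark, the number of breath-holds behind each position and the reference day all change with the time-point. Each time-point has one kind of measurement, so the data cannot separate method from change.

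The Statistical analysis section does not limit the comparison to the shared axis, say how three planes become one number, or say whether the treatment mean is the inter- or the intra-fraction value. R_BH at planning and at treatment are both primary outcomes. At stake is the conclusion that reproducibility seen at screening is, or is not, maintained through planning and treatment.

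**Working it through.** **The plan's own figure, and the room it leaves.** The article gives "required recruitment of 14–27 participants to be powered to detect a 2 mm variation in reproducibility". The lower number goes with an SD of 2 mm and the upper with 3 mm. Alpha and power are not stated. An exact paired t test for 2 mm gives 13 and 26 at two-sided 0.05 with 90% power, and exactly 14 and 27 at two-sided 0.0167 with 80% power. The range is therefore consistent with a paired comparison.

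If those SDs are of the paired difference (an assumption), the 95% half-width is:

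- n = 14, SD 2 mm: 2.16 × 2/√14 = 1.15 mm
- n = 27, SD 3 mm: 2.06 × 3/√27 = 1.19 mm

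The interval lies inside ±2 mm only if the observed mean difference is below 2 − 1.15 = 0.85 mm, or 2 − 1.19 = 0.81 mm, in absolute value. A method artefact of about 0.8 mm can decide the result.

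**Model with no true change.** Assumptions: cranio-caudal positions of single breath-holds are independent and normal with SD σ at every time-point; each planning CT reflects one breath-hold; a CBCT position is the mean of k breath-holds; R_BH is the mean absolute displacement. The starting value of 1.5 mm is the ABC expiration figure cited in the Background, used for illustration only. The article gives neither k nor the SDs of the other axes.

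*Pre-planning.* The difference of two breath-holds has variance 2σ², so E|D| = √(2/π) × √2 × σ = 1.128σ. A value of 1.5 mm means σ = 1.5/1.128 = 1.33 mm.

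*Planning.* On the cranio-caudal component alone the expectation is the same, 1.5 mm, and there is no artefact. As a three-plane vector with equal SDs, the ratio is 1.596/0.798 = 2.00, giving 3.0 mm. With the other two axes at half the cranio-caudal SD, simulation gives 3.12/2.26 = 1.38, so 1.5 × 1.38 = 2.07 mm.

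*Intra-fraction, cranio-caudal.* Both positions are averaged: variance 2σ²/k, factor 1/√k.

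*Inter-fraction, cranio-caudal.* Only the CBCT side is averaged: variance σ²(1 + 1/k), factor √((1 + 1/k)/2).

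| k (assumed) | Intra-fraction, from 1.5 mm | Inter-fraction, from 1.5 mm, no day-to-day shift |
|---|---|---|
| 2 | 1.06 mm | 1.5 × 0.866 = 1.30 mm |
| 3 | 0.87 mm | 1.5 × 0.816 = 1.22 mm |
| 4 | 0.75 mm | 1.5 × 0.791 = 1.19 mm |

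*Day-to-day shift.* If the cranio-caudal position shifts between planning and treatment days with SD τ, the inter-fraction variance is σ²(1 + 1/k) + τ². It returns to 2σ² when τ² = σ²(1 − 1/k). At k = 4 this is τ = 0.866 × 1.33 = 1.15 mm. A smaller shift leaves inter-fraction R_BH below screening; a larger one puts it above.

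**Simulation check** (200,000 draws, σ = 2 mm, k = 4, no shift, other axes at 0.5 to 1.0 times σ):

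| Measurement | Mean R_BH | Minus pre-planning (2.25 mm) |
|---|---|---|
| Planning, cranio-caudal | 2.26 | about 0 |
| Planning, vector | 3.12 to 4.52 | +0.87 to +2.27 |
| Inter-fraction, cranio-caudal | 1.78 | −0.47 |
| Inter-fraction, vector | 2.46 to 3.57 | +0.21 to +1.32 |
| Intra-fraction, cranio-caudal | 1.13 | −1.12 |
| Intra-fraction, vector | 1.56 to 2.26 | −0.69 to +0.01 |

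The differences are of the order of the margin, and their sign depends on choices the article leaves open.

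**The case against.** The strongest reply is that the article nowhere states a vector sum. Reporting plane by plane is at least as natural a reading, it supplies the cranio-caudal component directly, and the axis artefact between pre-planning and planning is then zero. A condensed article may also leave the choice of component to the full protocol or SAP. This stands against any claim that planning R_BH will be inflated. It does not remove the mismatch at treatment, where reference day, image type and breath-hold averaging differ even on one axis.

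The second reply is that the comparison is meant to be modest. The margin is hedged as an indication, Bland–Altman plots are planned, differences over time are to be assessed descriptively, and the study is called a pilot. That is partly right, but the same text still calls ±2 mm a non-inferiority margin and treats the differences as change over time.

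Stronger readings that a reader might infer, and why the document does not support them:

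- *Treatment R_BH is biased downward, towards non-inferiority.* The √k shrinkage applies in full only to intra-fraction R_BH. Inter-fraction R_BH shrinks less, and day-to-day shift adds to it.
- *A doubling of breath-hold variation would go unseen.* At k = 4 this holds for intra-fraction R_BH. For inter-fraction R_BH without day-to-day shift it holds only if treatment-day variation alone doubles (σ² + 4σ²/4 = 2σ²). If variation at the planning CT doubles too, the variance is 4σ² × 1.25 = 5σ², and 1.5 mm would read 1.5 × √(5/2) = 2.37 mm.
- *The correlations are invalid.* A constant rescaling leaves a correlation unchanged, and asking whether a one-axis screening measure tracks later imaging is legitimate.
- *Pre-planning usually tracks the diaphragm.* Only the abstract suggests this; the methods also allow the tumor or a fiducial.

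**Conclusion.** The point holds: the four R_BH measurements are not interchangeable, and judging their paired differences against one ±2 mm margin does not separate measurement from change. This rests on the article's own definitions and needs no assumed figure.

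The size does rest on assumptions. From 1.5 mm with nothing truly changed, planning R_BH would read 1.5 mm (cranio-caudal only) to 3.0 mm (isotropic vector). At an assumed k of 4, intra-fraction R_BH on the cranio-caudal axis would read 0.75 mm, and inter-fraction R_BH 1.19 mm before day-to-day shift. The net inter-fraction direction is unknown. Against about 0.8 mm of room inside the margin, itself conditional on the stated SDs applying to the paired difference, such artefacts could decide a conclusion. The comparison should be changed before analysis; the correlations and plots need no change.

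**What to change.** Amend the Statistical analysis section as follows.

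1. For every ±2 mm comparison across time-points, use the cranio-caudal component only, as mean absolute displacement with the same formula each time, of the structure tracked at pre-planning where it is visible on the later images.
2. Report the other planes and the OARs separately, outside that comparison.
3. Compare inter-fraction and intra-fraction R_BH separately, the latter only in participants with multiple CBCTs.
4. Report CBCT-based comparisons with estimates and intervals, but draw no non-inferiority conclusion against ±2 mm, because CBCT positions blend several breath-holds.
5. Keep the correlations and Bland–Altman plots.

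Matching the CBCT averaging with a pre-planning value built from averages of k breath-holds is not a direct alternative. Two disjoint averages need 6 or 8 breath-holds at k = 3 or 4, and only five exist per technique. The number of breath-holds per CBCT is also not among the items the article lists as recorded; Treatment efficiency counts those used to deliver treatment.

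The cost is analysis wording and, where the pre-planning structure was not otherwise measured, one more measurement on images already acquired. The article does not say that the diaphragm is visible on every CBCT, so some participants may drop out of a comparison. The downside is that the formal comparison covers one axis and treatment results no longer carry a non-inferiority claim.
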